##### Participants

Clusters (primary health centres in the two Valencian Health Departments) will be randomised to use the PDA or usual care by using a computer-generated list based on the number of collaborating general practitioners. Based on a logistic regression, a cluster size of 12 clusters, each enrolling 30 patients (360 observations), will achieve 80% power (95% CI) to detect a mean difference of 0.35 between the groups in decisional conflict scores. Patients will be considered candidates for screening by their clinicians according to the European Society of Urology recommendations [23].

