### 2.2. Data Collection

The study coordinator will enrol health care centres (clusters), and general practitioners will enrol patients. We will provide clinicians with one education session on the rationale for SDM in each centre. The intervention (PDA) will be applied at the cluster level to avoid contamination. Patients will be blind to the group designation. Factors influencing outcomes will be assessed at three levels: the health centre cluster, individual general practitioner and patient. The clinicians in the control group will proceed as in usual care. A research assistant blinded to the group assignment will collect information on patients’ demographic and clinical characteristics and on whether a PSA test was ordered from the medical records. A follow-up telephone survey of the patients will be conducted within 3 weeks of the visit in order to assess: (a) whether screening took place; (b) knowledge regarding prostate cancer (Knowledge of the Prostate Cancer tool [26]); (c) decisional conflict (ten-question Decisional Conflict Scale [27]) and (d) discussions regarding screening between patients and clinicians and the satisfaction with the screening decision (Satisfaction with Decision Scale [28]).

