### 2.3. Statistical Analysis

Patients’ and general practitioners’ characteristics between clusters will be analysed using the *t* test or Wilcoxon rank sum test for the continuous variables and the χ^2^ test for the categorical variables. Modified Poisson regression with a sandwich estimator for standard errors will be used to estimate the relative risk, accounting for clustering by site using fixed effects.

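### With 12 centres randomised whole, the site fixed effects must be dropped, and the named sandwich standard error then needs a small-sample method to keep type I error near 5%

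*Protocol article*

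**What the plan says.** All references are to the protocol article.

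- **Analysis (section 2.3, Statistical Analysis).** The method named for the relative risk is "Modified Poisson regression with a sandwich estimator for standard errors". On the dependence between patients of one centre, the same sentence describes the model as "accounting for clustering by site using fixed effects". The text does not say whether the sandwich is computed over patients or over centres, and it names no reference distribution or small-sample correction.
- **Level of the intervention (section 2.2, Data Collection).** "The intervention (PDA) will be applied at the cluster level to avoid contamination". Every patient in a centre therefore belongs to the same arm.
- **Size (section 2.1.4, Participants).** The plan has "a cluster size of 12 clusters, each enrolling 30 patients (360 observations", with 80% power to "detect a mean difference of 0.35 between the groups in decisional conflict scores".
- **Allocation (same section).** Centres "will be randomised to use the PDA or usual care by using a computer-generated list based on the number of collaborating general practitioners". The number of centres per arm is not given.

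**The concern.** A sandwich variance relies on having many independent units. Here the independent units are the 12 centres, not the 360 patients. Section 2.3 assigns the clustering to site fixed effects, but in a parallel cluster trial these absorb the arm contrast and have to go. What is left is the named sandwich, in one of two plain forms. Clustered on centre, its variance is biased low with so few clusters, and a normal reference ignores that about 10 degrees of freedom are available. Computed over patients, which is the usual form in modified Poisson regression, it takes no account of clustering.

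Both forms err in the same direction: p-values too small and intervals too narrow. For outcomes analysed as relative risks (section 2.3 does not list them; whether a PSA test was ordered is the obvious candidate), an aid with no effect would be declared effective more often than the nominal 5%. Correcting the collinearity alone would leave an analysis that runs and looks sound but rejects too often.

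**Working it through.** **Inputs from the article.** 12 centres, 30 patients each, 360 in total; intervention at centre level; 80% power; a 95% confidence level, read as two-sided alpha 0.05.

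**Assumed, because the article does not give them.** Arm split 6 vs 6 (5:7 and 4:8 also tried); ICC 0 to 0.10; event rate 0.3 or 0.5; cluster-size coefficient of variation (CV) 0 or 0.5; SD of the decisional conflict score.

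**1. The plan's own figure.** With 180 per arm and design effect DE = 1 + 29 × ICC, SE = SD × √(2 × DE/180) and power = Φ(0.35/SE − 1.96).
- SD 1, ICC 0: SE = 0.1054, 0.35/SE = 3.32, power 91.3%.
- SD 1, ICC 0.014: DE = 1.406, SE = 0.1250, 0.35/SE = 2.80, power 80%.
- SD 1.185, ICC 0: SE = 0.1249, power 80%.

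The 80% can be neither confirmed nor refuted without the SD and ICC. It concerns a mean score, so it gives no support for or against the relative-risk analysis.

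**2. Are the site effects compatible with an arm effect?** Twelve site indicators plus one arm indicator make 13 columns. The arm column is the sum of the indicators of the centres in that arm, so the rank is 12. The arm coefficient is not estimable.

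**3. Arm-only model, sandwich clustered on centre, normal reference.** With 6 equal centres per arm, the sandwich divides the between-centre sum of squares by 6 instead of 5, so the variance is 5/6 of what it should be. The degrees of freedom are 12 − 2 = 10.
- Type I error = 2 × P(t10 > 1.96 × √(5/6)) = 2 × P(t10 > 1.789) = 10.4%.
- Interval width relative to the width needed = 1.789/2.228 = 0.80.

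Simulation under the null (beta-binomial clusters, 40,000 replicates per scenario):

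| Scenario | Type I error |
|---|---|
| 6 vs 6, equal sizes | 9.5–10.4% |
| 6 vs 6, size CV 0.5 | 11.1–12.3% |
| 5:7, equal sizes | 10.0–10.9% |
| 4:8, equal sizes | 11.8–12.4% |

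The result hardly moves with ICC or event rate. A cross-check with standard GEE software (1,500 replicates) gave 10.9%.

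**4. Arm-only model, sandwich over patients.** Ignoring DE, type I error ≈ 2 × [1 − Φ(1.96/√DE)].

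| ICC (assumed) | DE | 1.96/√DE | Formula | Simulation, 6 vs 6, equal sizes |
|---|---|---|---|---|
| 0 | 1.00 | 1.960 | 5.0% | 4.7–5.2% |
| 0.01 | 1.29 | 1.726 | 8.4% | 8.4–8.7% |
| 0.02 | 1.58 | 1.559 | 11.9% | 11.6–12.3% |
| 0.05 | 2.45 | 1.252 | 21.0% | 20.6–21.1% |
| 0.10 | 3.90 | 0.992 | 32.1% | 32.2–32.4% |

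**5. Which corrections are enough?** Same simulation, 6 vs 6, sandwich clustered on centre:

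| Method | Equal sizes | Size CV 0.5 |
|---|---|---|
| 12/11 factor only, normal reference | 8.3–9.0% | 9.7–10.9% |
| t(10) only | 6.2–6.9% | 7.5–8.5% |
| Kauermann-Carroll with t(10) | 4.4–4.9% | 5.2–6.0% |
| Mancl-DeRouen, normal reference | 5.1–5.7% | 5.6–6.2% |
| Mancl-DeRouen with t(10) | 3.1–3.4% | 3.5–4.0% |

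The last row agrees with theory. In the balanced case Mancl-DeRouen inflates the variance by about 6/5, so 2 × P(t10 > 2.228 × √(6/5)) = 2 × P(t10 > 2.441) = 3.5%. The corrections are therefore not interchangeable once a t reference is added.

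**The case against.** The strongest objection is that the article does not describe an uncorrected analysis. It is silent on bias correction, reference distribution and degrees of freedom. Such details are commonly left to a statistical analysis plan, which is not at hand. This stands: a reader might infer that the sponsor has chosen an uncorrected sandwich, and the text does not support that inference. What remains is that the method as named, applied in its plain form to the stated 12 centres, does not hold its level. The sentence in section 2.3 also says how clustering is to be handled, and that way cannot work.

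Second, the model as written has no type I error of 10%, because with site effects in it there is no arm estimate. This also stands. The figures describe the analysis once the site effects are gone, and the two defects must be mended together. Site could conceivably mean the two Health Departments, whose effects would be estimable. But the article defines its clusters as the primary health centres, and department effects would leave clustering by centre unaddressed.

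Third, 6 centres per arm is an inference. That is so, but the uneven splits tried give similar or slightly worse results.

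Fourth, the patient-level figures depend wholly on assumed ICCs, and at ICC 0 there is no inflation. That is correct, and it is why a range is shown.

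Fifth, the trial is powered on a mean decisional conflict score, and the simulations cover a binary outcome only. A reader might infer that the trial's powered comparison has a 10% false-positive rate. Nothing here shows that.

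**Conclusion.** The point holds conditionally. The site fixed effects cannot stay if a relative risk for the aid is to be estimated; this follows from the design and needs no assumption beyond site meaning health centre. Once they are removed, the plain sandwich is too optimistic with 12 centres. Clustered on centre with a normal reference, type I error is about 10% instead of 5% and intervals are about 20% too narrow, assuming a 6 vs 6 split and equal sizes; uneven splits or sizes take it to about 12%. Computed over patients, type I error runs from about 5% at ICC 0 to 32% at ICC 0.10, with every ICC assumed. The finding is limited to outcomes analysed as relative risks. It does not establish that the sponsor has ruled out a correction.

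**What to change.** Amend section 2.3, and carry the change into the analysis plan:

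1. Remove the site fixed effects from the model for the intervention effect.
2. State that the sandwich is clustered on health centre.
3. Name one small-sample method suited to 12 clusters together with its reference distribution. Kauermann-Carroll with t on 10 df gives a type I error of 4.4 to 6.0% at 6 vs 6. Do not offer several corrections as equivalents: Mancl-DeRouen with t(10) is conservative, at about 3.5%.
4. Add a centre-level t test or a permutation test on the 12 centres as a sensitivity analysis.

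This costs a few sentences and a software option, and section 2.4 places the project at the design of its knowledge surveys, well before the trial phase. The statistical price is wider intervals: about 25% wider than the plain centre-clustered ones in the balanced case (1/0.803 = 1.245), with the corresponding loss of apparent precision.

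### Fixed effects for site, read as the randomised health centre, leave the PDA effect unidentified because each centre lies wholly in one arm

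*Protocol article*

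**What the plan says.** Three parts of the protocol article bear on this.

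- **Unit of randomisation** (Phase 4, Participants): "Clusters (primary health centres in the two Valencian Health Departments) will be randomised to use the PDA or usual care". The planned size is 12 centres of 30 patients.
- **Delivery** (2.2 Data Collection): "The intervention (PDA) will be applied at the cluster level to avoid contamination". The same section identifies the clusters as the health care centres that the study coordinator enrols.
- **Effect analysis** (2.3 Statistical Analysis): "Modified Poisson regression with a sandwich estimator for standard errors will be used to estimate the relative risk", followed by "accounting for clustering by site using fixed effects".

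This regression is the only between-arm effect analysis that the article states. It describes no crossover, stepped wedge or other variation of allocation within a centre, and it names no random centre effect or GEE as an alternative.

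**The concern.** Fixed effects for centre absorb every difference between centres. In a parallel cluster-randomised trial the treatment comparison is itself a difference between centres, so once each centre has its own free level nothing is left from which to estimate the PDA effect. The sandwich estimator does not help: it changes standard errors, not what the model can identify.

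Two things are at stake. The relative risk may be missing or arbitrary, in a way that depends on column order or solver rather than on the data. And any standard error from such a model describes variation between patients within centres, whereas centres were randomised and variation between centres is the yardstick that inference needs.

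**Working it through.** **Inputs.** From the article: 12 centres, 30 patients each, allocation by centre, modified Poisson model with site fixed effects. Assumed, because the article gives none of them: a 6-v-6 split, the event rate and the intracluster correlation (ICC). Step 1 needs none of these assumptions.

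**The plan's own figure.** 12 × 30 = 360 is correct. The 80% power for a 0.35 difference in decisional conflict cannot be confirmed or refuted without an SD and an ICC, and it plays no part below.

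**Step 1: identification.** Write log μ = α + βA + γ_j for a patient in centre j, with A = 1 in PDA centres. Add any constant c to β and subtract c from γ_j in every PDA centre: all fitted values stay the same, so β cannot be determined. In matrix terms, A is the sum of the PDA centres' indicators. The columns number 1 + 1 + 11 = 13. The centre indicators alone already have rank 12, and adding arm leaves the rank at 12. The R-squared of arm on the centre indicators is 1.0. This holds for any number of centres and any allocation ratio.

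**Step 2: what a fit may return.** In one simulated dataset (12 × 30, 6 v 6), events out of 30 were 18, 14, 16, 11, 16, 16 in PDA centres (total 91) and 9, 11, 8, 13, 11, 10 in control centres (total 62). The crude relative risk is 91/62 = 1.47. Forcing a fit by dropping one further centre indicator makes the arm coefficient a contrast of two reference centres. Over the 36 possible pairs it ran from 11/13 = 0.85 to 18/8 = 2.25, all with the same log-likelihood (−279.414). Two other outcomes are possible:

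- Software that removes later aliased columns drops arm if arm is entered after the centres.
- A pseudo-inverse solver drops nothing. On another simulated dataset it gave a log relative risk of 0.294 against a crude 0.279, which is a solver artefact.

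**Step 3: the error term, for illustration only.** Take a 50% event rate and a contrast of one centre against one. With independent patients the variance of the log relative risk is 2 × (1 − p)/(mp) = 2 × 0.5/(30 × 0.5) = 0.0667, so the SE is 0.258. Clustering multiplies the true variance by 1 + 29 × ICC. The approximate false-positive rate at nominal 5% is 2Φ(−1.96/√(1 + 29 × ICC)).

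| ICC | Variance factor | Approximate rate | Simulated rate (40,000 replicates) |
|---|---|---|---|
| 0.01 | 1.29 | 8% | 8.7% |
| 0.05 | 2.45 | 21% | 22.1% |
| 0.10 | 3.90 | 32% | 34.3% |

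At a 30% event rate the simulated figures are 6.7%, 19.2% and 29.9%. At 50% and ICC 0.05 the simulated SD of the log relative risk is 0.45 for one centre against one, compared with 0.17 for six against six.

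**Step 4: site read as Health Department.** Intercept, arm and one department indicator make 3 columns of rank 3 when both arms occur in each department, so the effect is identified. In the Step 2 dataset, with the sandwich clustered on centre, the relative risk was 1.47 (SE of the log 0.091). With no department term it was also 1.47 (SE 0.090).

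**Step 5: the remedy with 12 centres.** Under the null, with arm as the only term and equal 6-v-6 clusters, the uncorrected centre-clustered z test rejected in 9.5% to 10.2% of simulated trials (ICC 0.01 to 0.10, event rates 30% and 50%). Multiplying the variance by 6/5 and using t on 12 − 2 = 10 df brought this to 4.4% to 4.9%.

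**The case against.** **Site is not defined.** The word appears as the analysis unit only in the Statistical Analysis section, and the Participants section also names a higher level, the two Health Departments. Under that reading the effect can be estimated (Step 4). This stands as a limit: non-identification is conditional on site meaning centre. The department reading is the weaker one, because the fixed effects are said to account for clustering and the clusters are defined as centres. Nor does it rescue the text as written, which does not say on what unit the sandwich is clustered.

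**A reader might infer that no fixed-effects model can estimate the PDA effect at all.** That goes too far. With centres nested in arm and sum-to-zero constraints, arm becomes the difference in mean centre log rates. The article states no such constraint, however, and the inference would still be invalid: simulated false-positive rates were 8.5%, 21.9% and 33.0% at ICC 0.01, 0.05 and 0.10 with a 50% event rate.

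**A reader might infer that the reported figure must be one centre against another, or that 22% is the plan's error rate.** Neither follows. The one-centre contrast is one of several outcomes, and its error rates rest on an assumed event rate, ICC and split.

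**A reader might also take the sentence "Factors influencing outcomes will be assessed at three levels: the health centre cluster, individual general practitioner and patient" to mean that the plan enters centre-level factors into this same regression.** It stands under Data Collection and does not say so, so it is not relied on here.

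**The analysis plan could settle it.** It could, but this is a stated method that conflicts with the stated design, not a detail left out. A plan that copied the sentence would inherit the fault.

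**Conclusion.** The concern holds, conditional on site meaning the randomised health centre, which the article's own definition of clusters supports. On that reading the stated model has 13 columns of rank 12 and does not identify the relative risk for PDA against usual care. That result is algebraic and needs no assumed figure. The false-positive rates of about 22% (ICC 0.05) and 34% (ICC 0.10) for a one-centre contrast only illustrate what is lost when between-centre variation is left out; they assume a 50% event rate and the 6-v-6 split and are not properties of the plan. If site means Health Department, the effect is estimable provided both arms occur in each department, and the fault becomes unaddressed correlation within centres unless the sandwich is clustered on centre. The sentence needs changing under either reading.

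**What to change.** In 2.3 Statistical Analysis, remove the fixed-effects clause and state instead that:

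- the relative risk is estimated by modified Poisson GEE clustered on primary health centre, or by a mixed model with a random intercept for centre, with arm as a fixed term;
- inference uses a small-sample correction suited to about 12 clusters, for example a bias-corrected sandwich variance with t on 10 df. Without it, the change replaces the present fault with a type I error of about 10% at nominal 5%;
- if Health Department is wanted as a fixed covariate, it is named as such, separately from the unit of clustering.

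**Cost.** One sentence and no extra data. The Study Status section says the team is only starting to design the knowledge surveys, so this can be settled long before Phase 4 outcomes exist. The downside is a wider interval. Relative to one that ignores between-centre variation, the standard error grows by √(1 + 29 × ICC): 1.14 at ICC 0.01, 1.57 at 0.05 and 1.97 at 0.10, with the small-sample correction on top. That width reflects the information that a trial of 12 randomised centres contains.

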### 2.4. Study Status

We are commencing the design of the knowledge surveys.

### 2.5. Ethics and Dissemination

The PROSHADE protocol was approved by the CEIC Sant Joan d’Alacant (20/041) on 8 January 2021. All participants will give oral/written informed consent prior to entry to the study by a member of the study team and will be made aware that participation is strictly voluntary. Participants may withdraw from the study at any time. The research adopts the principles of open science, and the findings will be published ensuring the participants’ confidentiality.

**Trial registration:** Clinical trials: NCT05187949 (https://clinicaltrials.gov/) (accessed on 1 July 2022).

## 3. Discussion

The complexity of decision making in oncology requires patients and clinicians to consider the benefits and risks of an increasing number of clinical options. In addition, patients and clinicians evaluate the options differently, and, therefore, they need new ways to evaluate all the relevant information and personal preferences to make an informed decision. SDM has been hailed as the key to successfully consider patients’ and clinicians’ preferences, and, consequently, researchers, clinicians, patients and health policy representatives have made a considerable effort to implement SDM in clinical practice [2]. Thus, this project will contribute to increasing the scientific knowledge on how to promote SDM in PC screening, often seen as a controversial decision in oncology.

Psychological factors have been negatively associated with preventive health behaviors such as cancer screenings. A previous systematic review aimed to evaluate the impact of cancer screening through patient-reported outcomes (PROs) assessment [29]. It showed that although the psychosocial impact of cancer screening is relatively low overall, even following false-positive test results, individuals with a higher risk of cancer tend to experience more symptoms of anxiety and distress during the screening process. Therefore, the results conclude that higher-risk individuals undergoing screening should be considered when carrying out prostate cancer screening.

In addition, the process carried out to develop this SDM strategy in PC screening could guide SDM research in other medical practice areas. There is little consensus on which PDA format is most effective, and it is a challenge to develop patient decision aids that can be routinely used in practice. In 2003, the International Patient Decision Aid Standards [24] established a consensus on quality standards between PDA developers. However, questions have been raised about its validity in practice. With this project, we will establish an empirical evaluation of this procedure, which is generically described, to develop a PDA. According to the available recommendations, we will assess patients’ and clinician’s decisional needs and knowledge to obtain a range of perspectives on the information that patients and clinicians need to have in order to have a maximal influence on SDM outcomes. Moreover, and given that gaps have been identified in presenting probabilistic PSA information to patients, we will contextualise relevant information for patients such as the likelihood of having a false-positive result, in order to help them in a decision according to their personal preferences. We will also systematically review the available literature about the barriers and facilitators of PC screening in primary care and develop an initial PDA prototype to be tested in the target population. Finally, we will assess the PDA implementation in clinical practice. To guarantee an adequate implementation in practice, we will measure key outcomes such as decisional conflict or patients’ satisfaction with the screening decision.

## 4. Challenges and Limitations

Study limitations include that the evaluation is focused on short-term outcomes, and we will not be able to assess the implementation of the PDA in long-term practice. However, to guarantee an adequate implementation in practice, we will measure key outcomes such as decisional conflict and patients’ satisfaction with the screening decision.

Patients will be involved in the conduct of this research. Promoting SDM in PC screening is not a straightforward task, and success will rely heavily on the interaction with the patients and healthcare workers during the entire research process. The inclusion of patients and clinicians in the design and development of the new decision aid will help foster ownership of the tool, which will help ensure a more sustained diffusion to clinical practice in the long term. The participation of scientific societies and the patient association ANCAP will also be crucial to this aim.

